## ABSTRACT

**Background:** Hypothermia in preterm infants during the immediate postnatal phase is associated with morbidity and mortality and remains an unresolved, worldwide challenge.

A list of interventions, including adequate room temperature, use of infant warmers, polyethylene bags/wrap, pre-heated mattresses, caps and heated and humidified gases, to prevent thermal loss at birth in very preterm infants has been recommended, but a certain percentage of very preterm infants are hypothermic at the time of the neonatal intensive care unit (NICU) admission suggesting that further measures are needed. While drying is recommended for the thermal management of infants with gestational age >32 weeks, this procedure is not indicated for very preterm infants who should be put in a plastic wrap immediately at birth without drying. However, such indication is based on studies comparing wrapping without drying vs. drying without wrapping, while the potential advantages of combining these interventions were not explored. We hypothesized that drying before wrapping could prevent heat loss immediately after birth and reduce hypothermia at NICU admission in very preterm infants.

*Objective:* The aim of this study will be to compare two modes of thermal management (plastic wrapping with or without drying) for preventing heat loss at birth in very preterm infants.

*Methods:* This is a multicenter, unblinded, randomized controlled trial comparing drying vs. not drying before plastic wrapping for the thermoregulation of very preterm infants at birth. After obtaining parental consent, all infants with estimated birth weight <1500 g and/or gestational age  $\leq 30^{+6}$  weeks will be assigned to be managed with or without drying before plastic wrapping. Room temperature and maternal temperature will be measured at the time of delivery. Patients allocated in both groups will be managed based on the current guidelines for neonatal resuscitation. The primary outcome measure will be the proportion of neonates in the normal thermal range (temperature 36.5-37.5°C) at NICU admission. Secondary outcome measures will be: proportion of neonates with hypothermia (<36.5°C and <36.0°C) at NICU admission; proportion of hyperthermic neonates (temperature >37.5°C) at NICU admission; temperature at 1 hour after NICU admission; proportion

of intraventricular hemorrhage; proportion of respiratory distress syndrome; proportion of late onset sepsis; proportion of bronchopulmonary dysplasia; mortality before hospital discharge.

**Trial registration:** the study will be registered in ClinicalTrials.gov after EC approval.

**Keywords:** delivery room, hypothermia, preterm infant, drying, plastic wrapping

**Funds:** this is a no-profit study. No funds have been planned for this study.

## Background

The maintenance of thermal homeostasis is a milestone in neonatology (1-4). A significant association between hypothermia at delivery and adverse neonatal outcomes has been clearly demonstrated (5-8), but the incidence of hypothermia in very preterm infants at the time of admission to neonatal intensive care unit (NICU) in Europe remains still high (8).

International guidelines for neonatal resuscitation suggest several interventions to prevent thermal loss at birth in very preterm infants, such as adequate room temperature, use of infant warmers, polyethylene bags/wrap, pre-heated mattresses, caps and heated and humidified gases (9,10). Nevertheless, a certain percentage of very preterm infants are hypothermic at the time of the NICU admission suggesting that, in addition to the actual standard of care, further interventions are needed (4,9,10).

While drying is recommended for the thermal management of infants with gestational age  $>32$  weeks (9,10), this procedure is not indicated for very preterm infants who should be put in a plastic wrap immediately at birth without drying. Of note, such indication is based on studies comparing wrapping without drying vs. drying without wrapping (11,12), following previous investigations on plastic wrapping which were not conducted in the delivery room environment (13,14). However, the potential advantages of combining those interventions (drying and wrapping) were not explored. To our knowledge, only one study investigated the role of drying before wrapping in the thermal management of preterm infants, and found comparable temperatures after birth in infants wrapped after being dried and in those wrapped without drying (15). No data are currently available for very preterm infants, who are at higher risk of heat loss due to evaporation (16). We hypothesized that drying before wrapping could prevent heat loss immediately after birth and reduce hypothermia at NICU admission in very preterm infants.

The “PICOT” question of this study is:

P: in very preterm infants,

I: does drying before plastic wrapping in the delivery room,

C: compared to standard of care (plastic wrapping without drying),

O: increase the percentage of infants in the normal thermal range (temperature 36.5-37.5°C),

T: at the time of admission to the NICU?

The objective of this study will be to compare two modes of thermal management (plastic wrapping with or without drying) for preventing heat loss at birth in very preterm infants.

## **Methods/Design**

### **Study design**

This is a multicenter, unblinded, randomized controlled trial comparing drying vs. not drying before plastic wrapping for the thermoregulation of very preterm infants at birth.

### **Setting**

The study will be conducted at 21 Italian Level III hospitals.

### **Inclusion criteria**

Infants satisfying the following inclusion criteria will be eligible to participate in the study:

1. Estimated birth weight <1500 g and/or gestational age  $\leq 30^{+6}$  weeks (and)
2. Inborn (and)
3. Parental consent; a written informed consent will be obtained by a member of the neonatal team involved in the study from a parent or guardian at the maternal admission to the Obstetric Department.

### **Exclusion criteria**

1. Major congenital malformations (i.e. cardiac disease, defects of abdominal wall, ...);
2. Outborn;
3. Parental refusal to participate to the study.

### **Procedure**

Written and oral information will be offered to parents by the attending physician at maternal admission to the obstetrical ward or before delivery. After obtaining parental consent, all infants with estimated birth weight <1500 g and/or gestational age  $\leq 30^{+6}$  weeks will be assigned to be managed with or without drying before plastic wrapping in the delivery room immediately after birth. Axillary maternal temperature will be measured by a digital thermometer (C202; Terumo,

Tokyo, Japan) about 30 minutes before delivery. Room temperature will be measured at the time of delivery by using a wall thermometer (Oregon Scientific RMR262) in all the study sites.

Patients allocated in both arms will be managed based on the current guidelines for neonatal resuscitation that include the following steps:

- Maintain room temperature at least 24°C;
- Delayed cord clamping (>30 seconds) in uncompromised infants;
- Place the neonate under the radiant infant warmer with the power output set at maximum;
- Cover the body with a plastic bag/wrap up to the shoulders (with or without drying according to the randomized assignment);
- Cover the head of the baby with a cap;
- Use a pre-warmed mattress (optional);
- Use heated and humidified gases (optional).

In case of assignment to the treatment arm, the infant will be dried with a pre-warmed towel before plastic wrapping. In case of assignment to the control arm, the infant will not be dried before plastic wrapping.

All the other interventions, including CPAP, mechanical ventilation, supplemental oxygen concentrations, administration of chest compressions and/or medications will follow the current guidelines for neonatal resuscitation and the decision will be taken by the neonatal team.

At the end of the stabilization, the patient will be transferred to the NICU in a transport incubator (with the temperature set at 37°C).

In all participants, axillary temperature will be measured at 3 time points with a digital thermometer (C202; Terumo, Tokyo, Japan): a) at the end of the stabilization (before leaving the delivery room); b) at NICU admission (primary outcome); and c) 1 hour after NICU admission. Duration of the study will be until the patient's discharge or death.

### **Primary outcome measure**

1. The primary outcome measure will be the proportion of neonates in the normal thermal range (temperature 36.5-37.5°C) at NICU admission.

### **Secondary outcome measures**

2. Proportion of neonates with hypothermia (temperature <36.5°C) at NICU admission;
3. Proportion of neonates with moderate-severe hypothermia (temperature <36.0°C) at NICU admission;
4. Proportion of hyperthermic neonates (temperature >37.5°C) at NICU admission;
5. Temperature at 1 hour after NICU admission;
6. Proportion of intraventricular hemorrhage (all grades and grade III-IV);
7. Proportion of respiratory distress syndrome (RDS);
8. Proportion of late onset sepsis;
9. Proportion of bronchopulmonary dysplasia;
10. Mortality before hospital discharge.

### **Generalizability**

The findings of this study will be important for other level III hospitals where the majority of high risk pregnancies are referred, but also for level I and II centers where, sometimes preterm infants are born. The generalizability of the study is based on the large number of participating centers, representing different realities and different approaches to the delivery room management of very preterm infants. Based on the results of the present study, we could speculate whether drying the infant at birth may have a role in increasing the proportion of very preterm in the normal thermal range at NICU admission. Furthermore, potential complications, such as hyperthermia will be strictly monitored and collected.

## **Sample size**

Based literature data (17), we hypothesize that the proportion of neonates in the normal thermal range at NICU admission could increase from 40% in the control arm to 55% in the intervention arm. With a power of 80% and an error I type of 0.05, the minimum sample size is estimated in 346 neonates (173 per arm). As the design is a stratified multicenter individually randomized trial, randomization is balanced and stratified on centers, and we expect no loss of power as a result of randomizing neonates by center (18). Sample size calculations were performed using R 4.1 software (R Foundation for Statistical Computing, Vienna, Austria) (19).

## **Recruitment**

Written and oral information will be offered to parents at maternal admission to the Obstetric Department by the attending physician. Informed written consent will be signed by a parent. A senior investigator will be available at all times to discuss concerns raised by parents or clinicians during the course of the trial.

## **Randomization**

Eligible infants will be randomly assigned to intervention or control arms in a 1:1 ratio according to a computer-generated, randomized sequence for each participating hospital. Infants of multiple pregnancies will be randomized as individuals. Randomization (with blocks of size 4-6) will be stratified by center. The randomized allocation will be concealed in double-enclosed, opaque, sealed, and sequentially numbered envelopes prepared at University Hospital of Padua. In the delivery room/operating room, the next sequential randomization envelope will be opened only when the neonate will be considered to be eligible by the attending operator. The assigned procedure will be then performed. Contamination between arms will not be allowed.

## **Blinding**

Due to the characteristics of the intervention, neither caregivers nor outcome assessors will be masked to treatment allocation. However, the statistician who will perform data analysis will be blind for treatment allocation. To minimize bias, strict criteria and definitions will be maintained during the trial.

### **Guidelines for Management**

Before starting the study, the PI of each hospital (and at least one local collaborator) involved in the study will participate to a meeting where all the details of the study protocol will be presented. The local neonatal resuscitation teams responsible of the delivery room management will be educated on the details of the protocol including temperature measurements in term of correct modality (axillary), time of the study, collection of the data.

### **Data collection**

Data will be recorded in a data sheet designed for this study. All data will be collected by an observer not involved in the care of the neonates. The following clinical information will be registered: eligibility, antenatal history, randomization, all data above listed in ‘Primary outcome measure’, ‘Secondary outcome measures’ sections. Further information will be collected on expected serious adverse events (SAEs). Personal information about potential and enrolled participants will be collected, shared, and maintained in order to protect confidentiality before, during, and after the trial by the local P.I. in a personal PC protected by password. The P.I. and the members of the steering committee located in Padua will have access to the final trial dataset.

### **Statistical analysis**

Analysis will be performed according to the “intention to treat” approach. In case of deviations from the protocol regarding the contamination between arms, a per-protocol analysis will be also performed and the conclusion will be drawn according to the results of both analyses. Continuous

data will be expressed as mean and standard deviation, or median and interquartile range. Outcome measures will be compared between the two arms using Chi-square test, Fisher's test, Student *t* test or Mann-Whitney test as appropriate (unadjusted analysis). Regression models (adjusted analysis) will be estimated to evaluate the effect of drying on the outcome measures, adjusting for participating centers and potential confounders (i.e. clinically relevant variables or unbalanced characteristics at baseline). Effect sizes will be reported as risk ratio or mean difference with 95% confidence intervals. A sub-analysis according to gestational age ( $23^{+0}$ - $27^{+6}$  and  $28^{+0}$ - $31^{+6}$  weeks) will be performed with exploratory purpose. A p-value less than 0.05 will be considered statistically significant. Statistical analysis will be performed using R 4.1 software (R Foundation for Statistical Computing, Vienna, Austria) (19).

### **Ethical considerations**

Written parental consent is necessary before enrollment of the patients in the study. We consider that there will be not risks for both study groups. Hypothermia as well as hyperthermia episodes will be strictly monitored in both groups.

### **Ethics Committee approval**

The study will be approved by the Ethics Committees for Human Investigation of the participating hospitals.

### **Compliance to protocol**

Compliance will be defined as full adherence to protocol. Compliance with the protocol will be ensured by the local PI and collaborators in each hospital; they will be responsible for local data collection. The local PI will weekly monitor the adherence to the study protocol and will input the patients' data in an electronic data sheet. Double data entry will be performed by 2 independent members at each center to promote data quality.

**Missing data**

Investigators and study staff will be trained on the importance of the completion of the study period of enrolled patients. Parents will also be informed about this crucial aspect to reduce dropout, and a local investigator will be available at each site anytime the parents may need further information or clarification during the study period.

**Data Safety and Monitoring Board**

Safety measures will include incidence, severity and causality of reported SAEs, represented by changes in occurrence of the expected common neonatal complications and the development of unexpected SAEs. SAE will be defined as unexpected death, severe hyperthermia (temperature  $>39^{\circ}\text{C}$ ) and hypothermia (temperature  $<35^{\circ}\text{C}$ ). All SAEs will be followed until complete resolution or until the clinician responsible for the care of the recruited patient considers the event to be chronic or the infant to be stable.

A monitoring board including an independent assessor (not involved in the study) from the Azienda Ospedale Università di Padova and assessors from each participating hospital will review all the deaths and adverse effects. If there is a reasonable suspected causal relationship with the intervention, SAEs will be reported to the Ethics Committee to guarantee the safety of the participants.

An interim analysis will be performed on the primary endpoint and SAEs from the first 100 infants enrolled. The interim analysis will be performed by the statistician, blinded for the treatment allocation, who will report to the principal investigator. The principal investigator will discuss the results of the interim analysis with the monitoring board and the trial will be ended in case of harm. Criteria for stopping for harm include: a statistically significant difference in the primary outcome between the treatment groups; a reasonable suspected causal relationship between the intervention and SAEs.

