## 6.5 Interim Analyses and Data Monitoring

A monitoring board will review all deaths and adverse effects, as described in the trial protocol.

An interim analysis will be performed on the primary endpoint and the serious adverse events (SAEs) from the first 100 infants enrolled. The interim analysis will be performed by the statistician, blinded for the treatment allocation, who will report to the principal investigator. The principal investigator will discuss the results of the interim analysis with the monitoring board and the trial will be ended in case of harm. Criteria for stopping for harm include: a statistically significant difference ( $p < 0.001$  according to Haybittle-Peto boundary or  $p < 0.0294$  according to Pocock boundary) (14) in the primary outcome between the treatment groups; a reasonable suspected causal relationship between the intervention and SAEs.

Stopping for futility and/or interim analysis for sample size adjustment are not planned.

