## 10 Safety Analyses

The trial protocol enlists unexpected death, severe hyperthermia (temperature >39°C) and hypothermia (temperature <35°C) as serious adverse events (SAEs). Occurrence of SAEs will be summarized as frequency with percentage and compared between arms using Chi Square test or Fisher's test.

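### The SAE definition does not match the protocol's stated safety measure, so the planned interim comparison omits grade III–IV haemorrhage and any death judged expected

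*Combined protocol and SAP*

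**What the plan says.** The protocol describes safety events in three ways.

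- **Stated measure.** The Data Safety and Monitoring Board section says the safety measures cover the incidence, severity and causality of SAEs, "represented by changes in occurrence of the expected common neonatal complications and the development of unexpected SAEs".
- **Definition.** The next sentence of that section says "SAE will be defined as unexpected death, severe hyperthermia" (above 39 °C) and hypothermia (below 35 °C).
- **Collection.** The Data collection section says "Further information will be collected on expected serious adverse events (SAEs".

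The definition is the one carried into the analyses. In the protocol, "An interim analysis will be performed on the primary endpoint and SAEs from the first 100 infants enrolled"; SAP section 6.5 says the same. Both documents give two criteria for stopping for harm: a significant difference in the primary outcome, and a reasonably suspected causal link between the intervention and SAEs. SAP section 10 (Safety Analyses) begins "The trial protocol enlists unexpected death, severe hyperthermia", adds hypothermia, and compares those events between arms by chi-square or Fisher's test.

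Three other provisions matter. Both documents say that the monitoring board reviews all deaths and adverse effects. Intraventricular haemorrhage (all grades and grade III–IV) and mortality before discharge are secondary outcomes, analysed under SAP section 9. Carers and outcome assessors are not masked (protocol, Blinding; SAP section 4.3).

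**The concern.** A change in the frequency of a common complication is a difference between arms. It is hard to recognise from individual cases in a population where such events occur anyway. The protocol names this kind of change as its safety measure, then defines SAEs so that no common complication can be one. Two of the three listed events are extremes of temperature, the variable behind the primary outcome. The only non-thermal item is a death that someone has classed as unexpected. That class has no definition and no named adjudicator, and the people closest to the infant know the arm.

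The interim look is the only planned comparison that can protect infants not yet enrolled: 346 − 100 = 246 of the planned total. Its stated purpose is to end the trial in case of harm. The protocol itself says that drying is not indicated for these infants under current guidance. If deaths or severe haemorrhages were accumulating unevenly, nothing in the planned interim analysis would have to show it.

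**Working it through.** The point is mainly textual. The arithmetic only shows what could and could not be learned at the interim.

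**1. The plan's own figure.** With 40% vs 55%, two-sided α = 0.05, 80% power and 1:1 allocation:

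n per arm = [1.960·√(2·0.475·0.525) + 0.842·√(0.40·0.60 + 0.55·0.45)]² / 0.15² = (1.384 + 0.588)² / 0.0225 ≈ 173, or 346 in total.

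This reproduces the stated size. It is not in dispute and supplies the denominators: about 50 per arm at the interim and 173 per arm at the end.

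**2. Tracing the two outcomes through the plan.**

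| Place | Deaths | Grade III–IV haemorrhage |
|---|---|---|
| Interim analysis (protocol, board section; SAP 6.5) | only if judged unexpected | not included |
| SAE-based harm criterion (same places) | only if judged unexpected | not included |
| SAP 10, Safety Analyses | only if judged unexpected | not included |
| Board review of deaths and adverse effects | all; by arm not stated | not named; by arm not stated |
| Final secondary analysis (SAP 3.2 and 9) | all before discharge, by arm, relative risk with 95% CI | by arm, relative risk with 95% CI |

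The omission is in the first three rows. The last row shows that it does not extend to the final analysis as a whole.

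**3. How many deaths might be missed.** The documents give no mortality rate, no haemorrhage rate and no share of deaths that would be called unexpected. All rates here are assumptions.

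Deaths in the SAE table = 100 × mortality × share called unexpected.

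| Assumed mortality | Deaths in first 100 | Counted if 10% / 25% / 50% / 75% called unexpected |
|---|---|---|
| 5% | 5 | 0.5 / 1.25 / 2.5 / 3.75 |
| 10% | 10 | 1 / 2.5 / 5 / 7.5 |
| 15% | 15 | 1.5 / 3.75 / 7.5 / 11.25 |

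The proportion left out is simply one minus the assumed share, so the table measures nothing about this trial. Grade III–IV haemorrhages counted as SAEs are zero at any rate, because they are not on the list.

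**4. What a by-arm table could show at 100 infants.** Power for a doubling of risk, two-sided 0.05, same normal approximation:

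| Assumed control rate | 50 per arm | 173 per arm |
|---|---|---|
| 5% | 16% | 42% |
| 10% | 29% | 74% |
| 15% | 43% | 92% |

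If both arms had the same rate p, the 95% CI half-width for the risk difference would be 1.96·√(2p(1−p)/50). That is 8.5 percentage points at p = 5% (1.96 × 0.0436), 11.8 at 10% (1.96 × 0.0600) and 14.0 at 15% (1.96 × 0.0714). The interim table can inform the board's judgement; it cannot support a reliable test.

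**The case against.** The strongest reply has four parts.

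- **The final analysis covers both outcomes.** This is correct. A reader might infer from SAP section 10 that deaths and severe haemorrhage are left out of the final comparison. They are not: SAP sections 3.2 and 9 compare both by arm. At the end of the trial, only the section headed Safety Analyses leaves them out.
- **The board reviews all deaths and adverse effects.** This also stands and is a real safeguard. Nothing limits that review to causality or to the SAE list. But neither document says that it is by arm, and the one interim analysis that is specified stops at the primary endpoint and SAEs.
- **The list includes the direct thermal harms of a thermal procedure.** It does, so it would be wrong to call the safety part of the interim analysis almost empty. The documents give no rates for these events either. The point is what the list leaves out relative to the protocol's own stated measure.
- **A table at about 50 per arm would rarely establish excess harm.** The power figures confirm this. It argues for a descriptive table, not for having none.

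Two other strong readings also fail. A reader might infer that most deaths would go uncounted; that needs a share of unexpected deaths which the documents do not give. A reader might also infer that treating clinicians decide what is unexpected. No section assigns the decision, and data are collected by an observer not involved in care. What can be said is that the term and the decision-maker are undefined, in a trial where outcome assessors are unmasked. The word *expected* in the Data collection section may mean only events foreseen by the protocol, but even so it does not fit a definition built on unexpected death.

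**Conclusion.** The concern holds for the interim look and for SAP section 10 (Safety Analyses). The stated safety measure, the SAE definition and the data-collection sentence do not agree. The interim analysis and the SAE-based harm criterion follow the narrow definition, so they omit every grade III–IV haemorrhage and any death judged expected. This follows from the text and needs no assumed rate.

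The number of deaths affected cannot be stated from the documents; the illustrative counts rest wholly on assumed mortality and an assumed share called unexpected. The final between-arm comparison of both outcomes is intact. This is an inconsistency in safety monitoring that should be corrected at little cost. It does not affect the primary analysis or the sample size.

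**What to change.** - **Reconcile the wording** of the protocol sections Data collection and Data Safety and Monitoring Board with SAP sections 6.5 and 10 (Safety Analyses), so that one description of safety events governs collection, interim analysis, harm criterion and final safety report.
- **Add a descriptive interim table for the board** showing deaths from any cause and grade III–IV intraventricular haemorrhage by arm, with counts, risk difference and 95% CI. Label it as descriptive. Because follow-up runs to discharge or death, also give the number of infants in each arm with complete follow-up at the data cut.
- **Cross-reference both outcomes in the SAP safety section** to their analysis in SAP section 9, without duplicating it.
- **If *unexpected death* is kept as an SAE category**, define it and say who decides it, without knowledge of the arm where possible.

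Which events count as SAEs remains a decision for the investigators; the table does not depend on it.

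The cost is a wording change in both documents and one more interim table. Both outcomes are already collected. The drawback is that the estimates will be imprecise at about 50 infants per arm, and the board should be told so.

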### 6.2 Approach for main analysis

Data analysis will be performed using the statistical software packages R. All tests will be two-sided and a p-value less than 0.05 will be considered statistically significant. Statistical analysis will include an unadjusted analysis followed by an adjusted analysis.

Analysis will be performed according to the "intention to treat" (ITT) approach. In case of deviations from the protocol regarding the contamination between arms, a per-protocol analysis will be also performed, and the conclusion will be drawn according to the results of both analyses.

Additional sub-group analyses will be considered with exploratory purpose.

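### The primary-outcome criterion for stopping for harm has no direction, so a significant benefit of drying at 100 infants would meet it as written

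*Combined protocol and SAP*

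**What the plan says.** The protocol (Data Safety and Monitoring Board) sets the look: "An interim analysis will be performed on the primary endpoint and SAEs from the first 100 infants enrolled". The principal investigator then discusses the results with the monitoring board, and "the trial will be ended in case of harm". One criterion for harm concerns the primary outcome: "Criteria for stopping for harm include: a statistically significant difference in the primary outcome between the treatment groups". The other is a suspected causal link between the intervention and SAEs. The protocol gives no p-value for this look.

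SAP 6.5 repeats the rule and attaches two levels to it, p<0.001 "according to Haybittle-Peto boundary" or p<0.0294 "according to Pocock boundary", without choosing between them and without naming the arm that must be worse. It adds: "Stopping for futility and/or interim analysis for sample size adjustment are not planned". A stop for benefit is not mentioned in either document.

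SAP 6.2 fixes sidedness: "All tests will be two-sided and a p-value less than 0.05 will be considered statistically significant". Direction is defined only for the final analyses. In SAP 8 a relative-risk interval above 1 favours drying on the primary outcome, and SAP 9 takes an interval below 1 as favouring drying on the binary secondary outcomes.

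On who performs the look, SAP 6.5 says: "The interim analysis will be performed by the statistician, blinded for the treatment allocation, who will report to the principal investigator".

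**The concern.** A harm rule has to say what counts as harm. Here the outcome is a good one and the criterion is any significant difference, so the result that the trial hopes to see satisfies the rule. The person who calculates the p-value does not know the arms. A two-sided p-value can be reported in that state, but harm cannot be judged until someone establishes which arm is worse, and no such step is written.

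If drying works as hypothesised, the board could be told that the harm criterion has been met at 100 of 346 infants (28.9% of planned enrolment). The observed effect would probably be exaggerated, and data on hyperthermia, intraventricular haemorrhage and death would be limited. The board would then have to override the plan's own words or end the trial under the wrong label.

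**Working it through.** **Inputs.**
- Normal-range proportion 40% (control) and 55% (drying), two-sided alpha 0.05, power 80%, 346 infants: protocol, Sample size; SAP 5.
- Interim at 100 infants: protocol, Data Safety and Monitoring Board; SAP 6.5.
- 1:1 allocation: protocol, Randomization. An exact 50/50 split at the interim is an assumption.
- Chi-square or Fisher's test: SAP 8.
- Interim levels 0.0294 or 0.001: SAP 6.5. The level 0.05 is used only as a reading of the protocol, which gives no interim level.

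**Step 1. Reproduce the plan's sample size.** With pooled variance under the null,

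n per arm = [1.96·√(2·0.475·0.525) + 0.842·√(0.40·0.60 + 0.55·0.45)]² / 0.15² = 172.8, rounded up to 173, or 346 in total.

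This agrees with the stated figure, so the design rates can be used as they stand.

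**Step 2. Results that meet the criterion.** Suppose 20/50 control infants are in the normal range. With 31/50 in the drying arm, the pooled proportion is 51/100 = 0.51, the standard error is √(0.51·0.49·2/50) = 0.100, z = 0.22/0.100 = 2.20 and p = 0.028. That meets the harm criterion at 0.0294 although drying is 22 points better. By chi-square, the smallest drying-arm counts that meet it are 30/50 at 0.05 (p = 0.046), 31/50 at 0.0294 (p = 0.028) and 37/50 at 0.001 (p = 0.0006).

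**Step 3. Chance of this under the design rates.** Sum Bin(x; 50, 0.40)·Bin(y; 50, 0.55) over all tables with p below the level, split by the sign of y − x:

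| Interim level | Benefit meets criterion, chi-square | Benefit meets criterion, Fisher | Harm direction, chi-square |
|---|---|---|---|
| 0.0294 (SAP) | 27.3% | 21.0% | about 0.01% |
| 0.001 (SAP) | 3.4% | 2.1% | <0.01% |
| 0.05 (protocol, if so read) | 34.4% | 27.3% | 0.03% |

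Among tables that cross at 0.0294 by chi-square in favour of drying, the mean observed difference is 27.0 points against a true 15.

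**Step 4. No true difference (40% in both arms, chi-square).** Crossings split evenly: 1.6% each way at 0.0294, 0.05% at 0.001 and 2.6% at 0.05.

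**Step 5. What a direction costs.** Suppose drying lowers the proportion by 15 points (40% versus 25%, an assumption). A rule limited to the harm direction triggers with probability 28.6% at 0.0294, 4.4% at 0.001 and 35.8% at 0.05 (chi-square). The undirected rule adds only crossings in the wrong direction, at most 0.02% in this scenario.

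**Step 6. If the rule also serves as a benefit stop.** With two looks correlated at √(100/346) = 0.538 and the final test kept at 0.05, the overall two-sided type I error is about 0.072 for 0.0294 at the interim, 0.0505 for 0.001 and 0.090 for 0.05.

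**The case against.** The strongest reply is that no reasonable board would stop for harm on a benefit. The operative condition is harm, a discussion with the board precedes any stop, and SAP 6.1 speaks of stopping at the board's suggestion. This stands in part. A reader might infer that a significant benefit would automatically end the trial. The documents do not support that, and the percentages above are chances of meeting the written criterion. It does not remove the defect, because a pre-specified rule should not depend on its readers correcting it.

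A reader might also infer that blinding makes a harmful effect impossible to identify. The documents do not support that either. Only the statistician is described as blind. Caregivers and outcome assessors are unmasked, nothing says the principal investigator or the board is masked, and the SAE criterion presupposes knowing who was dried. What is missing is a described step, not the possibility.

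A third reply is that the rule is really a two-sided boundary mislabelled as a harm rule: SAP 6.5 names two group-sequential boundaries and cites a paper whose title concerns stopping for benefit. This is plausible. The remedy would then be to separate the two purposes, not necessarily to give up a benefit stop.

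Finally, the size depends on the threshold. The 34.4% figure needs the 0.05 level, whereas SAP 6.5 sets its own interim levels. At p<0.001 the chance is only 2–3%. That is correct, but the SAP leaves 0.0294 equally available.

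**Conclusion.** The concern holds in this form: as written in both documents, a significant benefit of drying at 100 infants meets the primary-outcome criterion for ending the trial for harm, subject to the board discussion. The SAP does not repair this, and SAP 13 states that it proposes no change to the protocol's statistical approach.

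Under the design rates the chance is about 21–27% at p<0.0294 and 2–3% at p<0.001. It is 27–34% only if the protocol's unspecified level is read as 0.05. Nearly every crossing in that scenario would be in favour of drying. These figures assume 50 infants per arm at the look and independent infants, and each range runs from Fisher's test to chi-square. The wording defect itself depends on none of these assumptions.

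**What to change.** In the protocol's Data Safety and Monitoring Board section and in SAP 6.5:

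1. State that the primary-outcome harm criterion is met only when the proportion in the normal thermal range is significantly lower in the drying arm than in the control arm.
2. Choose one of the two SAP boundaries and give it in both documents.
3. State separately whether a stop for benefit is allowed. If it is, give its boundary and the matching final significance level.
4. Have the statistician report results coded A/B, with the board's independent assessor holding the key and establishing the direction before the rule is applied. This keeps the statistician blind, as planned.

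The cost is a few sentences in each document, settled before the interim look. It needs no extra infants or data, and step 5 of the working shows essentially no loss of protection against harm.
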